### Survival Assessment

Overall survival will be determined from the date of start of treatment to the date of death irrespective of the cause of death. At the end of the study a survival follow up report for each patient is required. Patients who have not died at the time of the final analysis will be censored at the date of last contact.

Time to progression and survival will be summarized using Kaplan-Meier methodology.

## Post-Treatment Assessments

After discontinuation of erlotinib treatment, patients will be followed for response duration, if still progression free and until disease progression according to protocol schedule. Any serious erlotinib related toxicity must continue to be reported until resolution or until no further change is expected.

## Quality of life

Karnofsky performance score, weight and FACT-L questionnaire will be assessed at baseline and at disease evaluation time points.

# Safety assessment

At 2 weeks after treatment initiation and subsequently at the disease evaluation time points.

- Physical examination, vital signs, weight, PS
- Adverse events NCI CTC version 3.0 grades
- Haematology, biochemistry including renal and liver function tests (ureum, creatinine, SGOT, SGPT, bilirubine levels).

# Study Design and Dosing Regimen

## Study Design

This is an open label non-randomized multicentre phase II trial in patients with advanced (inoperable stage III or IV) NSCLC (adenocarcinoma) who have tumour material available for EGFR mutation analysis and in whom a kinase domain mutation has been identified.

## Dosing Regimen

**The first dose of erlotinib must be given within 1 week after establishment of a gene mutation.**

The mutation status will be communicated via the central data management to the participating investigators. All enrolled patients will receive erlotinib (150 mg/day). No dose escalation of erlotinib is permitted. Erlotinib will be dose reduced for toxicities as detailed in section 12. Toxicity will be graded according to the NCI CTCAE v3.0. Treatment may be delayed for ≤ 2 weeks to allow recovery from toxicity.

Patients will be treated until progression of disease or unacceptable toxicity.

## Study Duration

The recruitment will continue until the number of patients foreseen has been accrued. Patients will remain on treatment until withdrawal due to toxicity, disease progression or withdrawal due to any other reason. The study will be terminated after every living patient has had a follow up of at least 6 months after stopping erlotinib, or when all patients have died.

## Administration of erlotinib

Erlotinib will be given on an outpatient basis at a fixed dose of 150 mg as a single daily oral dose. Dosage is not based upon body weight or body surface area. Prescribed daily dose is to be taken preferably in the morning, with up to 200 mL of water. Drug should be taken at least 1 hour before or 2 hours after the ingestion of any food or other medications, including grapefruit juice, vitamins and iron supplements.

Missed daily doses should be skipped. Doses should be taken at the same time each day. If the patient vomits after taking the tablets, the dose is replaced only if the tablets can actually be seen and counted. If a patient misses a dose normally taken in the morning, s/he may take the dose any time during that same day. However, the missed dose should not be taken on a subsequent day.

## Description and handling of erlotinib

For a description of handling, drug formulation, packaging and storage see the TarcevaTM Investigators Brochure, which will be provided by F HOFFMANN-LA ROCHE.

## Drug Accountability

Free drug is made available for this study by and directly delivered to the investigators, after confirmation of inclusion by the central data office.

Drug accountability logs record quantities are received directly from F HOFFMANN-LA ROCHE.

Quantities dispensed to patients, including lot number, date dispensed, patient identifier number, patient initials, protocol number, dose, quantity returned, batch number, expiry date and the initials of the person dispensing the medication has to be maintained per institutional standards.

# Safety Issues

Safety will be evaluated by collection of all serious adverse events and adverse events leading to premature withdrawal. In addition, unexpected erlotinib related AEs and erlotinib related rash must be reported. An unexpected AE is one which specificity or severity is not consistent with the current version of the erlotinib Investigator’s Brochure.

Severity should be recorded and graded according to the NCI CTCAE, v3.0. The CTC manual can be found at the following website

<http://ctep.cancer.gov/reporting/ctc.html>

A drug-related AE is defined as, a noxious and unintended response to any dose of a drug product for which there is a reasonable possibility that the product caused the response.

This criterion, in addition to good clinical judgment, should be used as a guide for determining the causal assessment.

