# Protocol synopsis

| **Title**  PROSPECTIVE EVALUATION OF SMALL MOLECULE EGFR-1 TYROSINE KINASE INHIBITION AS A FIRST-LINE TREATMENT IN PATIENTS WITH ADVANCED NON-SMALL CELL LUNG CANCER (NSCLC) HARBOURING A MUTANT EGFR GENE |
| --- |
| **Sponsor / Study Coordination**  Dienst Medische Oncologie - Oncologisch Centrum  Academisch Ziekenhuis Vrije Universiteit Brussel |
| **Study hypothesis**  Erlotinib is a safe and effective first-line treatment for NSCLC harboring a mutant EGFR |
| **Study design**  One arm, multicenter investigator initiated phase II study. |
| **Primary objective**  To investigate the efficacy and feasibility of using a small molecule EGFR inhibition in the first-line treatment of non-small cell lung cancer carrying (a) EGFR kinase domain mutation(s) not amenable to curative treatment. |
| **Primary endpoint**  Progression free survival time. |
| **Secondary objectives**  Objective response rate according to the RECIST criteria, metabolic response rate Feasibility, toxicity, duration of response and survival (TTP and OS from the date of study entry). |
| **Secondary endpoints**   - Toxicity according to the NCI-CTCAEv3 criteria. - Feasibility (reported descriptively). - Duration of response - Overall survival (from the initiation till PD). |
| **Patient selection criteria**   - - **Identification of an EGFR TKD mutation in the tumor material of the patient.** - No previous chemotherapy for metastatic disease. - Patients in whom any other anticancer treatment is needed after inclusion in the study will be considered to have met the primary endpoint. - Standard phase II recruitment criteria. |

| **Treatment plan and special procedures**  Patients will remain in the study under continuous treatment with erlotinib as long as they remain progression free, receive no other secondary anticancer treatment and remain free from unacceptable toxicity. |
| --- |
| **Study treatment duration, discontinuation and study withdrawal**   - At any time during study, progression of disease, unacceptable toxicity or patient refusal will result in study treatment discontinuation. - Patients that stop study treatment for other reasons than progressive disease must be followed by serial assessment of their response status as provided by the protocol |

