## Supportive care measures

### Diarrhea

Diarrhoea has been commonly observed (~ 50%) and is usually transient in nature. Previous trials have shown that the frequency and severity of diarrhoea rarely hindered administration of erlotinib and could be managed with loperamide. The recommended dose is loperamide 4 mg at first onset, followed by 2 mg q 2 – 4 hours until diarrhoea free for 12 hours.

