### Schedule of Assessments

Table 4.

|  | **Screening/**  **Baseline**  **Maximum days prior to first treatment** | **Treatment Period**  **Timing** | **End of Study** |
| --- | --- | --- | --- |
| Informed Consent | 3 weeks | - | - |
| Demographics | 3 weeks | - | - |
| Medical history | 3 weeks | - | - |
| Physical examination | 3 weeks | Every 6 weeks | X |
| Pregnancy test1 | 48 hours before starting erlotinib | - | - |
| Laboratory2 | 2 weeks | Every 6 weeks | X |
| Tumor measurements3 | 2 weeks | - On day 14.  - Then every 6 weeks from treatment initiation, up to 6 months of follow-up  - Thereafter q 12 weeks | X |
| Tumor Biopsy and mutation analysis 4 | pretreatment |  |  |
| ECOG Performance Status | 7 days | Every 6 weeks | X |
| erlotinib administration |  | Continuously | - |
| Safety5 | - | Recorded throughout study | X |
| Survival | - | - | X |

1. In women of childbearing potential only
2. Hematology: Hemoglobin, WBC, granulocytes and platelet count, INR (Only for patients receiving warfarin or coumadin-derivative. To be done twice per week during for 3 weeks; then weekly or more often as clinically indicated.) Biochemistry: Alkaline phosphatase, Serum bilirubin, Serum creatinine, AST (SGOT) and ALT (SGPT). Only laboratory abnormalities linked to unexpected clinical symptoms will be documented in the CRF.
3. CT scans, MRI or X-ray as per Institutional Standards and FDG-scan (appendix 5 for CT-scan and FDG-scan specification). The first FDG scan is at day 14. It is also proposed that a CT-scan is performed at the same time point.
   For responding patients, a confirmatory evaluation should be repeated at least 4 weeks (normally at the next 6 week interval evaluation) after the initial determination of response.
4. A formaline fixed paraffin tissue block representative of the patient's primary cancer at the initial diagnosis or a pretreatment bronchoscopy biopsy or a biopsy from a metastatic site will be sent to the Laboratory of Molecular Oncology, Oncology Centre, AZ-VUB.
5. Serious Adverse Events, Adverse Events leading to premature withdrawal, unexpected erlotinib related AEs and erlotinib related rash.

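### The protocol contradicts itself on which adverse events are recorded; under its restrictive text, expected non-serious toxicity such as diarrhoea would be under-reported against the CTCAE endpoint

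*Protocol*

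**What the plan says.** **Text without restriction by event type**

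- Section 3 (synopsis) lists as a secondary endpoint "Toxicity according to the NCI-CTCAEv3 criteria". It also states the hypothesis "Erlotinib is a safe and effective first-line treatment for NSCLC harboring a mutant EGFR".
- Section 10 (Safety assessment) lists "Adverse events NCI CTC version 3.0 grades", together with haematology and biochemistry, at 2 weeks and at the disease evaluation time points.
- Section 12.6 sets the period for collecting adverse events, from recruitment to 30 days after the end of treatment. It names no categories.

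**Restrictive text**

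- Section 12 (Safety Issues): "Safety will be evaluated by collection of all serious adverse events and adverse events leading to premature withdrawal". It continues: "In addition, unexpected erlotinib related AEs and erlotinib related rash must be reported".
- Section 12.9, Table 4 footnote 5, defines the Safety row as "Serious Adverse Events, Adverse Events leading to premature withdrawal, unexpected erlotinib related AEs and erlotinib related rash". The clinical assessments list under the recording formalities in the same section gives the same four categories.
- Section 12.9, Table 4 footnote 2: "Only laboratory abnormalities linked to unexpected clinical symptoms will be documented in the CRF".
- Section 12.3 asks for the CRF's adverse event form for erlotinib-related events that the Investigator's Brochure does not describe.

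**The concern.** A toxicity endpoint by CTCAE grade needs the graded events in the database. Section 12.5 names diarrhoea and skin rash as the most common effects of erlotinib, but only rash is on the four-category list. Section 12.3 lists diarrhoea, nausea, vomiting, fatigue, stomatitis, dry eyes and liver test abnormality as expected. Such events therefore reach the list only if they are serious, end treatment, or are more severe than the Brochure describes.

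Three things are at stake.

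- **Bias.** A toxicity table built on the restrictive text would understate the milder, expected toxicity. Sections 5 and 15 use the favourable tolerability of this drug class as part of the case for the trial, so the understatement falls where evidence would be most useful.
- **Inconsistency between sites.** The trial is multicentre. A site following Section 10 and a site following Section 12 would record different data, and a pooled rate would mix the two.
- **No later repair.** This is data collection, so it cannot be left to an analysis plan. Events that were never entered cannot be analysed.

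**Working it through.** The protocol gives no sample size, threshold or error rate for safety, so it has no figure to reproduce. The check is which events fall through, and how many.

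**Step 1. Follow one event through the rules.** Take an erlotinib-related grade 3 diarrhoea managed without hospital admission.

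- Serious? Not necessarily. Section 12.2 itself separates severity from seriousness.
- Leading to withdrawal? Not by Table 3, where grade 3 diarrhoea leads to interruption and restart at a reduced dose. Grade 4 leads to discontinuation and so would be captured.
- Unexpected? Diarrhoea is on the expected list in Section 12.3. It would be unexpected only if its severity went beyond the Brochure, which is not at hand.
- Rash? No.

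Such an event can change treatment and still be off the list in Section 12 and Table 4 footnote 5. Section 10 would have it graded. The two instructions give different databases.

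**Step 2. Expected number with diarrhoea.**

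- Planned number of patients, n = 40 (Section 15).
- Rate p of about 0.50, from Section 12.7: "Diarrhoea has been commonly observed (~ 50%) and is usually transient in nature".
- Expected count = n × p = 40 × 0.50 = 20. For the 33 and 35 patients also named in Section 15, it is 16.5 and 17.5.
- If all were recorded and 20 of 40 were seen, the exact 95% interval would be 33.8% to 66.2%.

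**Step 3. Number recorded under the restrictive text.** Let s be the share of diarrhoea cases that are serious or lead to withdrawal. The protocol gives no value, so s is an assumption and is varied. Recorded count = 20 × s; apparent rate = 0.50 × s.

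| Assumed s | Patients recorded (of about 20) | Apparent rate in 40 |
|---|---|---|
| 2% | 0.4 | 1% |
| 5% | 1 | 2.5% |
| 10% | 2 | 5% |
| 20% | 4 | 10% |

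If some sites followed Section 10 and others Section 12, with a share f of patients at the former, the pooled apparent rate would be 0.50 × [f + (1 − f) × s]. With s = 2% this runs from 1% (f = 0) to 50% (f = 1). The result would depend on how sites read the protocol.

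**Step 4. Non-serious grade 3 events.** Suppose an expected grade 3 event that is neither serious nor withdrawal-causing has a true rate of 5% to 15% (an assumption).

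- Expected count: 40 × 0.05 = 2 to 40 × 0.15 = 6 patients.
- Chance of at least one: 1 − 0.95^40 = 0.87 to 1 − 0.85^40 = 0.998.

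At such rates, at least one would probably occur and stay off the list.

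**The case against.** The strongest reply is that the restriction is not settled. Sections 10 and 12.6 are unrestricted, and a site following Section 10 would grade every event. That stands: it makes this a contradiction to be resolved and not a uniform rule. It does not remove the problem. The four-category list appears three times, and footnote 2 is the only text that says which laboratory findings reach the CRF.

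A reader might also draw stronger conclusions that the document does not support:

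- **That the toxicity endpoint and the safety hypothesis cannot be answered at all.** Serious events, withdrawals for toxicity, unexpected related events and rash are all collected, and Section 12 requires CTCAE grading. The serious part of the profile can be described. The safety hypothesis also carries no threshold that the missing data would defeat.
- **That the commonest events would be nearly absent.** This is untrue of rash, which Section 12.7 puts above 50% and which is explicitly collected. For diarrhoea, the recorded share depends on s, which the protocol does not give.
- **That no expected grade 3 event would be recorded.** The seriousness criteria in Section 12.1 include medically significant events, and unexpectedness in Sections 12 and 12.2 takes account of severity. Some grade 3 events could qualify.
- **That the efficacy decision is affected.** Better tolerability enters Section 15 as a prior premise. The trial's toxicity data play no part in the 50% and 70% rule, and this single-arm trial plans no toxicity comparison with chemotherapy.
- **That the timing of adverse event recording conflicts.** Table 4 has Safety recorded throughout the study. The week-2 mismatch with Section 10 concerns physical examination, performance status and laboratory tests only.

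**Conclusion.** The point holds as an internal contradiction with a predictable direction of bias. The CTCAE endpoint in the synopsis and the collection described in Sections 10 and 12.6 do not agree with the four-category list in Sections 12 and 12.9, nor with footnote 2 on laboratory findings. Under the restrictive text, rates by grade of expected, non-serious, non-rash toxicity would be too low. That includes those grade 3 events that are neither serious nor unexpected and do not end treatment.

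For diarrhoea the gap is about 20 of 40 patients against about 0.4 to 4 recorded, or 50% against 1% to 10%. The 50% and the 40 are the protocol's figures; the 2% to 20% behind the lower numbers is assumed. The CRF itself is not at hand, so this is a finding about the written instructions. It should be corrected, but it does not threaten the primary endpoint.

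**What to change.** Reconcile Section 12, Section 12.3, Table 4 footnotes 2 and 5, and the recording formalities in Section 12.9 with the synopsis endpoint and Section 10:

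- The CRF records adverse events with the worst CTCAE v3 grade per evaluation. Recording all events is simplest. All related events plus all events of grade 3 or higher would be a workable minimum.
- The CRF records the CTCAE grade of the laboratory tests already being performed, in place of the limit in footnote 2.
- The four-category list is kept for expedited reporting only, and is labelled so.

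Separately, reconcile the week-2 physical examination, performance status and laboratory tests in Section 10 with the 6-weekly timing in Table 4.

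The cost is more data entry for about 40 patients. The recording change needs no new test or visit and alters no dose or management rule.

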## Serious Adverse Events

A serious adverse event is any experience that suggests a significant hazard, contraindication, side effect or precaution. It is any adverse event that at any dose fulfils at least one of the following criteria:

- is fatal (results in death) (unless clearly due to disease progression) (note: death is an outcome, not an event)
- is life-threatening (note: the term “life-threatening” refers to an event in which the patient was at risk of death at the time of the event; it does not refer to an event which could hypothetically have caused death had it been more severe)
- required patient hospitalization or prolongation of existing hospitalization (note: “inpatient hospitalization” refers to an unplanned, overnight hospitalization)
- results in persistent or significant disability/incapacity
- is a congenital anomaly/birth defect
- is medically significant or requires intervention to prevent one or other of the outcomes listed above

Medical and scientific judgment should be exercised in deciding whether expedited reporting to the Coordinator is appropriate in other situations, such as important medical events that may not be immediately life-threatening or result in death or hospitalization but may jeopardize the patient or may require intervention to prevent one of the outcomes listed in the definitions above. These situations should also usually be considered serious. Examples of such events are intensive treatment in an emergency room or at home for allergic bronchospasm; blood dyscrasias or convulsions that do not result in hospitalization; or development of drug dependency or drug abuse.

## Handling of Serious Adverse Events

Any adverse event that is considered SERIOUS must be reported within one working day by the investigator to the central data office, which will also inform the Roche. Roche is still responsible for reporting SAEs to the authorities, in any countries where there are ongoing trials involving erlotinib (erlotinib)

An unexpected adverse event is one, of which the nature or severity is not consistent with the safety information in the investigator’s brochure.

Investigators must assess the causal relationship between the event and the study drug. There are only 2 possibilities:

- “NO” no reasonable suspicion of a causal relationship
- “YES” reasonable suspicion of a causal relationship

The term severe is a measure of intensity, thus a severe adverse event is not necessarily serious. For example, nausea of several hours' duration may be rated as severe, but may not be serious.

A serious adverse event occurring during the study, or which comes to the attention of the investigator within 28 days after stopping the treatment, whether considered treatment-related or not, must be reported. In addition, a serious adverse event that occurs after this time, if considered related to the study medication, should be reported.

On request from the sponsor such preliminary reports will be followed by detailed descriptions later, which will include copies of hospital case reports, autopsy reports and other documents.

The Serious Adverse Event should be reported on the SAE form which can be found as an attachment to the CRF and should be faxed to the central data office contact specified below.

**<Datamanagement>**

**<[name]>**

**<Oncologisch Centrum>**

**<AZ-VUB>**

**<[contact]>**

**<[contact]>**

**Contact for SAEs:**

1. The central data management office by [contact] and/or email ([[name];[contact]](mailto:[contact])) and/or [contact]
2. The local institutional ethical committee (within the first 24h of the following weekday).

The investigator must notify his/her Ethics Review Committee/Institutional Review Board of a serious adverse event in writing as soon as is practical and in accordance with international and local laws and regulations.

The investigator should report all pregnancies in the study within 24 hours to the same central datamanagement office, using the form for Serious Adverse Events. On receipt of this form, a special pregnancy follow-up form will be provided for the documentation of relevant data (ante-natal ultrasound, health of baby, etc.). This form must be returned within 24 hours of any fatal anomaly being detected, or as soon as possible after a normal birth.

## Expected Adverse Event

The most common, expected AEs for erlotinib include: rash (dermatosis), diarrhea (with or without dehydration), nausea, vomiting, fatigue, stomatitis, headache, and dry eyes. Less frequent but more severe events include infections without neutropenia, liver function test abnormality, INR elevation, GI hemorrhage, and rare reports of interstitial lung disease. For a complete list of expected AEs, please see the current version of the erlotinib Investigator’s Brochure.

Erlotinib related AEs not described in the erlotinib Investigator’s Brochure, regardless of seriousness should be reported on the Adverse Event Report Form included in the CRF.

## Pregnancy

A female subject must be instructed to stop taking the test “drug” and immediately inform the investigator if she becomes pregnant during the study. Pregnancies occurring up to 90 days after the last dose of the test “drug” must also be reported to the investigator. (add if approprThe investigator should report all pregnancies within 24 hours to the principle investigator. The investigator should counsel the subject; discuss the risks of continuing with the pregnancy and the possible effects on the foetus. Monitoring of the patient should continue until conclusion of the pregnancy.

Pregnancy occurring in the partner of a subject participating in the study should also be reported to the investigator and the sponsor. The partner should be counselled and followed as described above.

